# A randomised open-label trial to assess outpatient induction of labour (HOMEIND) and compare efficacy of Propess vs Dilapan-S® for induction of labour at 39 weeks’ gestation in normal risk nulliparous women: study protocol for a randomised controlled trial

**DOI:** 10.1186/s13063-023-07174-7

**Published:** 2023-02-23

**Keywords:** Induction of labour, Outpatient induction, Dilapan-S, Propess, Induction, Elective induction of labour, Cervical priming, Osmotic dilator, Cervical ripening

## Abstract

**Background:**

Induction of labour (IOL) at 39 weeks has been shown to decrease maternal and neonatal adverse outcomes. Given the growing demand for 39-week IOL, it is imperative that effective methods be assessed for induction in the outpatient setting.

The aim of this study is to answer the clinical question as to whether Dilapan-S® vs Propess® as a method of cervical ripening is non-inferior in the outpatient setting at 39 weeks and to ascertain whether Dilapan-S® 12 h is non-inferior to Dilapan-S® 24 h.

**Methods:**

This study is an open-label parallel group single-centre *randomised* trial.

Participants are normal risk nulliparous women who have no pregnancy-related or medical contraindication to IOL. Women will be randomised to one of three induction groups—Dilapan-S® (12-h insertion or 24-h insertion) or Propess. Induction will be initiated between 39+0 and 39+4 weeks’ gestation and participants will return home for either 12 or 24 h. They will be readmitted 12/24 h later in order to continue with induction of labour.

Patient recruitment will take place over 30 months within a single centre. The study will recruit a maximum 109 women for each study arm. Total duration of participants’ involvement in the trial will be 8 weeks to allow for postpartum follow-up.

**Discussion:**

This study will definitively answer whether Dilapan-S is non-inferior to Propess® as a method of induction of labour in the outpatient setting and whether cervical ripening with Dilapan-S over a 12-h timeframe is non-inferior to cervical ripening with Dilapan-S over a 24-h timeframe.

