#### Secondary objective(s)

To compare the Dilapan-S® (12 h) group to the Propess group in the primary endpoint and secondary endpoints.To compare the Dilapan-S® (24 h) group to the Propess group in the primary endpoint and secondary endpoints.To compare the Dilapan-S® (12 h) group to the Dilapan-S® (24 h) group in the primary endpoint and secondary endpoints.To compare rates of vaginal delivery in the Dilapan-S® 12-h group, the Dilapan-S® 24-h group, and the Propess group at 36 h, 48 h, and 48 h respectively from insertion time to delivery. 

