#### Sample size {14}

A single primary comparison will be used to determine efficacy. The sample size was therefore revised, from a potentially under-powered study of two co-primary comparisons, to an adequately powered study of a single primary comparison.

A 10% margin was used as the non-inferiority margin for the treatment comparison of Dilapan-S (combined groups) versus Propess. SVD rates were assumed to be 70%, 75%, and 80% in the Propess, Dilapan-S® (24 h), and Dilapan-S® (12 h) groups, respectively. Assuming 90% statistical power, a one-sided 2.5% level of statistical significance, and equal treatment group allocation, the study sample size required is 285 for a per-protocol analysis. Allowing for a 15% non-adherence rate, the total required recruitment is 327 (109 per group) for the intention-to-treat analysis. Other treatment comparisons will be considered secondary and exploratory.

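### The abstract promises a definitive 12-h versus 24-h Dilapan-S non-inferiority answer, but the design treats that comparison as exploratory and neither sets a margin for it nor powers it

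*Protocol article*

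**What the plan says.** Two parts of the abstract make 12 h versus 24 h a non-inferiority question for this trial. The Background gives as part of the aim "to ascertain whether Dilapan-S® 12 h is non-inferior to Dilapan-S® 24 h". The Discussion opens with "This study will definitively answer whether Dilapan-S is non-inferior to Propess® as a method of induction of labour in the outpatient setting" and, in the same sentence, extends the promise to "whether cervical ripening with Dilapan-S over a 12-h timeframe is non-inferior to cervical ripening with Dilapan-S over a 24-h timeframe".

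The body of the article ranks the comparison differently:

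- **Sample size {14}:** "A single primary comparison will be used to determine efficacy". The 10% margin is given "for the treatment comparison of Dilapan-S (combined groups) versus Propess", and the 90% power and the sample size follow from that comparison. On everything else: "Other treatment comparisons will be considered secondary and exploratory". The section adds that a plan with two co-primary comparisons was given up as potentially under-powered. It does not say which two comparisons these were.
- **Secondary objective(s):** "To compare the Dilapan-S® (12 h) group to the Dilapan-S® (24 h) group in the primary endpoint and secondary endpoints". This asks for a comparison and does not mention non-inferiority.
- **Primary objective (Objectives {7}):** non-inferiority of Dilapan-S to Propess, with both insertion times named in parentheses.

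**The concern.** A comparison cannot be both definitively answered and exploratory. Non-inferiority also has no meaning until a margin is fixed, and the only margin in the article belongs to a different contrast. A reader of the abstract alone would expect a confirmatory conclusion about the shorter insertion time, which the design was not built to give.

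A smaller, related issue concerns the primary objective. Because it names both insertion times, a positive pooled result could be quoted as non-inferiority of either regimen. The planned test concerns the two arms combined, and the sample size section itself assumes different rates for them (80% and 75%).

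**Working it through.** **Inputs (Sample size {14}):** assumed rates of 70% for Propess, 75% for Dilapan-S 24 h and 80% for Dilapan-S 12 h; margin 10 points for combined Dilapan-S versus Propess; one-sided 2.5%; 90% power; equal arms; 285 per protocol (95 per arm) and 327 recruited (109 per arm). Per-protocol is the main analysis set and intention-to-treat is supportive (Statistical methods {20a}).

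**Step 1. Reproduce the plan's own figure.** The combined Dilapan-S rate is (75% + 80%)/2 = 77.5%, with 190 women against 95. The distance to the margin is 0.10 + 0.775 − 0.70 = 0.175.

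- Pooled variance: mean rate (0.70 + 2 × 0.775)/3 = 0.75. SE = √[0.75 × 0.25 × (1/95 + 1/190)] = 0.0544. Power = Φ(0.175/0.0544 − 1.96) = 89.5%. Exactly 90% would need 291 women.
- Unpooled variance: SE = √[0.70 × 0.30/95 + 0.775 × 0.225/190] = 0.0559. Power = 87.9%, and 90% would need 306.

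The stated 285 is therefore reproduced closely, within about 2% on the pooled formula. The primary comparison has roughly the power claimed for it.

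**Step 2. Apply the same rule to 12 h versus 24 h.** The article gives no margin here, so the 10-point margin is borrowed as an assumption. With n per arm,

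Power = Φ[(0.10 + p12 − p24)/SE − 1.96], SE = √{[p12(1 − p12) + p24(1 − p24)]/n}.

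| True rates (12 h, 24 h) | n per arm | SE | Power |
|---|---|---|---|
| 80%, 75% (protocol's own) | 95 | √(0.3475/95) = 0.0605 | Φ(0.15/0.0605 − 1.96) = 69.9% |
| 80%, 75% | 109 | √(0.3475/109) = 0.0565 | 75.7% |
| 75%, 75% (reviewer's scenario) | 95 | √(0.3750/95) = 0.0628 | Φ(0.10/0.0628 − 1.96) = 35.6% |
| 75%, 75% | 109 | √(0.3750/109) = 0.0587 | 39.9% |

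Simulation of the 95% confidence interval rule gives 70.3%, 76.2%, 36.1% and 40.4%, in the same order.

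**Step 3. Sensitivity to the borrowed margin, 95 per arm.**

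| Margin (points) | Both 75% | 80% vs 75% |
|---|---|---|
| 5 | 12% | 38% |
| 7.5 | 22% | 54% |
| 10 | 36% | 70% |
| 12.5 | 51% | 83% |
| 15 | 67% | 91% |

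Only a 15-point margin together with a true 5-point advantage for 12 h reaches the 90% planned for the primary comparison.

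**Step 4. Size that would be needed.** At a 10-point margin, 90% power requires (1.96 + 1.2816)² × 0.3475/0.15² ≈ 163 per arm under 80% vs 75%. If both rates are 75%, it requires (1.96 + 1.2816)² × 0.3750/0.10² ≈ 395 per arm. The trial caps recruitment at 109 per arm.

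**Step 5. Expected precision.** At 95 per arm the 95% confidence interval half-width is about 1.96 × 0.0628 = 12.3 points with equal rates, or 1.96 × 0.0605 = 11.9 points at 80% vs 75%. With equal observed rates near 75%, the interval would extend beyond a 10-point margin.

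**The case against.** The strongest reply is that the operative text is already right. The sample size section fixes one primary comparison and labels the rest exploratory, and the secondary objectives only ask for a comparison. On that view the fault is confined to the abstract. This is largely correct, and it limits the point to a claim that must be restated; the primary analysis is not defective. It does not remove the conflict, because the abstract states the aim and the promise in plain terms.

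A second reply is that a margin for a secondary contrast may sit in the analysis plan, which is not shown. That stands: the missing margin alone would be no finding. But a margin set there would not turn an exploratory contrast into a definitive one.

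A third reply is that the power figures depend on choices the article does not make. That also stands. They borrow a margin, and the lower figures use equal rates, whereas the protocol assumes a 5-point advantage for 12 h. They should be quoted only with those conditions.

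A reader might go further and infer that pooling would hide a regimen that is itself inferior to Propess. With true rates of 85% (12 h), 60% (24 h) and 70% (Propess), simulation at 95 per arm does declare pooled non-inferiority in 59% of trials. The documents do not support using this as the size of the problem. It needs a 25-point gap between regimens where the protocol assumes 5. Pooling is openly stated, and each regimen versus Propess is listed among the secondary objectives, so a poor regimen would be visible.

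**Conclusion.** The abstract claims a property that the design does not have. The 12-h versus 24-h comparison is exploratory by the protocol's own statement, and the article gives it neither a margin nor planned power. With a borrowed 10-point margin and one-sided 2.5%, power is about 70% (95 per arm) to 76% (109 per arm) under the protocol's assumed 80% vs 75%, and about 36% to 40% if both true rates are 75%. These figures illustrate the gap; the contradiction holds without them.

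The stated sample size for combined Dilapan-S versus Propess reproduces closely, and nothing here challenges that comparison. A positive result on it supports the combined strategy. It does not by itself establish non-inferiority of either insertion time.

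**What to change.** 1. In the abstract's Background and Discussion, limit the definitive wording to combined Dilapan-S versus Propess. Describe the 12-h versus 24-h difference as exploratory, estimated with a 95% confidence interval.
2. In the abstract's Discussion and in the primary objective, say that a positive primary result supports non-inferiority of the combined Dilapan-S strategy only. Report each regimen versus Propess as an exploratory estimate with a 95% confidence interval, in line with the sample size section.

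This needs no extra patients, no alpha and no change to the primary analysis. The cost is a more modest stated claim.

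Adding a fixed sequence of regimen-level tests after the pooled test is not recommended as a simple repair. It would make confirmatory two contrasts that the protocol calls exploratory, and the statistical methods section already makes a superiority test conditional on non-inferiority. If both branches hang on that gate at full one-sided 2.5% with no order between them, error is not controlled. With true rates of 60% (12 h), 80% (24 h) and 70% (Propess) and 95 per arm, simulation gives at least one false claim (pooled superiority or 12-h non-inferiority) in 3.4% of trials. If regimen-level confirmatory claims are wanted, their tests and the superiority test would have to be placed in one prespecified order.

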### Statistical methods

#### Statistical methods for primary and secondary outcomes {20a}

The analysis of the primary outcome will use a confidence interval (95% level of confidence) for simple differences in proportions. Non-inferiority will be determined on the lower confidence interval limit (equivalent to a one-sided 97.5% confidence interval). Conditional on non-inferiority being demonstrated, superiority will be determined. The analyses will be performed in the per-protocol population, supported by an intention-to-treat analysis.

Secondary outcomes will be compared using confidence intervals and hypothesis tests. However, these will be considered exploratory in nature. No adjustment for multiple testing will be performed.

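### The abstract promises a definitive non-inferiority answer for Dilapan-S 12 h versus 24 h, but the sample size section makes that comparison exploratory, with no margin or power of its own

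*Protocol article*

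**What the plan says.** In the protocol article, the abstract's Background gives a two-part aim. The second part is "to ascertain whether Dilapan-S® 12 h is non-inferior to Dilapan-S® 24 h". The abstract's Discussion opens with "This study will definitively answer whether Dilapan-S is non-inferior to Propess® as a method of induction of labour in the outpatient setting", and the same sentence extends the promise to "whether cervical ripening with Dilapan-S over a 12-h timeframe is non-inferior to cervical ripening with Dilapan-S over a 24-h timeframe".

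The body is more modest. The primary objective under Objectives {7} concerns Dilapan-S against Propess. The dwell-time question appears under Secondary objective(s) as "To compare the Dilapan-S® (12 h) group to the Dilapan-S® (24 h) group in the primary endpoint and secondary endpoints", with no non-inferiority wording.

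Sample size {14} states "A single primary comparison will be used to determine efficacy" and explains that the design was revised to this from two co-primary comparisons that might have been under-powered. It does not name the comparison that was dropped. It then says "A 10% margin was used as the non-inferiority margin for the treatment comparison of Dilapan-S (combined groups) versus Propess" and closes with "Other treatment comparisons will be considered secondary and exploratory".

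Recruitment is capped at 109 women per arm in the abstract's Methods and in Trial design {8}.

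**The concern.** The abstract gives the 12 h versus 24 h question the same confirmatory standing as Dilapan-S versus Propess. The sample size section withdraws that standing: the margin, the power and the confirmatory status all belong to the pooled comparison.

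Dwell time is the only thing that separates two of the three arms, so readers may choose a regimen on this answer. The abstract is also the text against which the trial report will be read. A non-inferiority conclusion needs a margin fixed in advance and enough women to exclude a loss of that size. The document gives neither for this comparison.

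**Working it through.** **Inputs, all from Sample size {14}:** assumed success rates of 70% (Propess), 75% (Dilapan-S 24 h) and 80% (Dilapan-S 12 h); 10-point margin; one-sided 2.5%; 90% power; equal allocation; 285 women per protocol (95 per arm); 327 recruited (109 per arm). The decision rule, the lower limit of a 95% confidence interval for a difference in proportions, is in section {20a}.

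**Step 1. Reproduce the stated 285.** The pooled Dilapan-S rate is (75 + 80)/2 = 77.5%, against 70%, with 2:1 allocation. The distance from the margin is 0.10 + 0.075 = 0.175. The Farrington–Manning method sets the null variance at rates restricted to differ by the margin, here 80.5% and 70.5%:
- null SD term: sqrt(0.805×0.195 + 0.705×0.295/2) = 0.511
- alternative SD term: sqrt(0.70×0.30 + 0.775×0.225/2) = 0.545
- n for Propess = [(1.96×0.511 + 1.2816×0.545)/0.175]² ≈ 94.3, rounded up to 95
- total = 95 + 190 = 285, an exact match

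The stated sample size is therefore the one required for the pooled comparison. No separate calculation is given for 12 h versus 24 h.

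**Step 2. Observed tie, 12 h versus 24 h.** The 10-point margin is borrowed here as an assumption. At a tie the lower limit is −1.96 × sqrt(2p(1−p)/n).

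| n per arm | both 75% | both 80% |
|---|---|---|
| 95 | −12.3 points | −11.4 points |
| 109 | −11.5 points | −10.6 points |

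All four lie beyond −10. Newcombe and score intervals, computed at the nearest whole counts, lead to the same conclusion. By the Wald interval a tie passes only if both observed rates exceed about 85.5% (95 per arm) or 82.9% (109 per arm).

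**Step 3. Power against the borrowed margin.** Power = Φ[(0.10 + d)/SE − 1.96], where d is the true 12 h minus 24 h difference and SE = sqrt{[p₁(1−p₁) + p₂(1−p₂)]/n}.

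| True rates (12 h v 24 h) | 95 per arm | 109 per arm |
|---|---|---|
| 75% v 75% | Φ(0.10/0.0628 − 1.96) = 36% | 40% |
| 80% v 80% | Φ(0.10/0.0580 − 1.96) = 41% | 45% |
| 80% v 75% | Φ(0.15/0.0605 − 1.96) = 70% | 76% |

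Exact binomial enumeration at 95 per arm gives 36%, 42% (0.415) and 70%.

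**Step 4. Size needed for 90% power.** n per arm = [p₁(1−p₁) + p₂(1−p₂)] × (1.96 + 1.2816)²/(0.10 + d)². This gives 395 (75% v 75%), 337 (80% v 80%) and 163 (80% v 75%), all above the cap of 109.

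**The case against.** The strongest reply is that this is abstract prose only. The primary objective, the secondary objectives and the sample size section agree with one another, and no sample size, allocation or primary test rests on the two sentences. That is correct, and it is why the remedy is confined to wording. It does not remove the contradiction.

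A second reply is that the analysis plan, which is not shown, may set a margin. It may, so the missing margin would be a weak point on its own. A margin set there would still leave the comparison exploratory under section {14}, and it could not add women beyond 109 per arm.

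Several stronger readings are tempting, and the document does not support them:
- *That the trial cannot show 12 h to be non-inferior.* The plan assumes 12 h is 5 points better. If 80% versus 75% were observed at 95 per arm, the lower limit would be 5.0 − 11.9 = −6.9 points, inside a 10-point margin. The assumed rates are also labelled as SVD rates, whereas the primary outcome counts operative vaginal delivery as success too, so observed rates could be higher than 75–80%. The comparison is underpowered, not incapable.
- *That section {20a} gives this comparison only a test of difference.* Its sentence "Secondary outcomes will be compared using confidence intervals and hypothesis tests" is about outcomes. The 12 h versus 24 h comparison includes the primary endpoint, for which the same section prescribes a confidence interval judged on its lower limit.
- *That a non-significant result will be published as non-inferior, or that type I error is inflated.* Nothing in the text forecasts such reporting. Extra error of up to about 4.9% (1 − 0.975²) would arise only if the comparison were treated as a second confirmatory claim, which section {14} rules out.

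**Conclusion.** The concern holds as a contradiction between the abstract and the sample size section: the abstract claims a confirmatory property that the design does not give to 12 h versus 24 h.

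The size of the gap depends on two assumptions: the 10-point margin, which the document sets only for the pooled comparison, and observed or true rates in the plan's own 75–80% range. On those assumptions, power at 95 per arm falls well short of the trial's 90% whether the regimens are truly equal or 12 h has the planned 5-point advantage. A tie would not meet the margin even in all 109 recruited per arm. A different margin would change these figures, but it would not reconcile the definitive and exploratory descriptions.

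**What to change.** In the abstract's Background and Discussion, replace the 12 h versus 24 h non-inferiority claim with wording such as: the trial will estimate the difference between Dilapan-S 12 h and 24 h in the primary endpoint, with a 95% confidence interval, as an exploratory comparison; a non-significant difference will not be interpreted as non-inferiority. The secondary objectives and section {14} already fit this and need no change.

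This costs two edited sentences and no additional women. The downside is a more modest claim.

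If the sponsor prefers a confirmatory statement, three things must be fixed in advance: a justified margin for this comparison; its power at the planned size (with 10 points, about 70% at 80% versus 75% and 36% at 75% versus 75%, for 95 per arm); and its position in a single fixed sequence. Section {20a} already places a superiority test after non-inferiority of the primary comparison. The order of the 12 h versus 24 h step relative to that superiority test must therefore be stated, because two branches each tested at the full one-sided 2.5% after the same gate would not control the error rate. Section {14} would then also have to drop the exploratory label for this comparison.

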**Trial registration:**

EudraCT Number 2019-004697-25 Registered 14 September 2020

## Administrative information

Note: the numbers in curly brackets in this protocol refer to SPIRIT checklist item numbers. The order of the items has been modified to group similar items (see http://www.equator-network.org/reporting-guidelines/spirit-2013-statement-defining-standard-protocol-items-for-clinical-trials/).

## Introduction

### Background and rationale {6a}

Induction of labour (IOL) has become a topical subject in recent years, with studies examining the role of IOL at certain gestations in achieving lower caesarean section rates, reduced neonatal morbidity and mortality rates, and improved maternal experience. These outcomes have been examined through RCTs and observational and qualitative studies amongst others.

It has been shown that IOL at 39 weeks’ gestation in otherwise uncomplicated (normal risk) nulliparous women decreases the primary caesarean section rate, is cost-effective, does not result in increased perinatal adverse outcomes, and may decrease some adverse outcomes [1–3]. This research has shown that pain scores were reported as lower, and perceived control scores (i.e. expectations and experiences of personal control during childbirth as measured with the Labor Agentry Scale) were reported as higher (indicating greater perceived control) with IOL at 39 weeks compared to expectant management [1].

What is not clear from the literature is whether there is a more effective method of achieving successful IOL in such patients at 39 weeks, and if the cervical ripening process can be managed outside of the hospital setting, ideally reducing resource utilisation and resulting in a more positive experience within the cohort being induced.

A vaginal dinoprostone delivery system (Propess or Cervidil) is a common method of cervical ripening for induction of labour, in which a delayed-release prostaglandin formulation is placed within the vagina. Dilapan-S is a synthetic osmotic hygroscopic gel which acts as a mechanical induction agent which has also been utilised in the setting of IOL and works by absorbing moisture from surrounding tissues to gradually dilate the cervix by expansion. Whilst both have been the subject of a number of studies assessing efficacy and safety, no trial has compared the efficacy of both in relation to each other at 39 weeks in the outpatient setting. Given the impact of the ARRIVE Trial, which suggests increased utilisation of IOL, and given the capacity restrictions on inpatient labour ward settings, there is now an urgent requirement to evaluate the optimal method of outpatient cervical ripening in order to support this likely increased demand.

The IND HOME trial aims to assess the two methods of IOL, both of which allow the patient to return home for 12 or 24 h after initiation. The primary outcome of the study is assessment of vaginal delivery by any means within a given time frame (36 h in the 12-h Dilapan-S® group and 48 h in the 24-h Dilapan-S® and Propess® groups), assessing suitability of both methods as cervical ripening agents in an outpatient setting.

